#### Circadian rhythms assessments

2.3.2

The sleep–wake cycle and body temperature, both strong circadian markers, will be evaluated using actigraphy and tympanic temperature measures.

The sleep–wake cycle will be continuously recorded over a 7-day using the Motion Watch 8 wrist-worn triaxial actigraph (CamNTech Ltd., Cambridge, United Kingdom). It is a highly reliable tool that has been validated for older adults (56, 57) and in the participant’s home living conditions (58). The Motion Watch Motion Ware software (Cambridge Neurotechnology Ltd., Cambridge England) combined with this actigraph will provide measures of TST (min) SOL (min); WASO (min); SE (%); sleep fragmentation index (SFI); and non-parametric circadian rhythm analysis [average of the Least active 5-h periods (L5, counts); average of the most active 10-h periods (M10, counts); Inter-daily Stability (IS); Intra-daily stability (IV); and Relative Amplitude (RA)].

Tympanic body temperature will be measured using a clinical thermometer (Braun ThermoScan^®^ 3). The temperature (in degrees Celsius °C) will be recorded over a 1 day, during the actigraphy period, with two readings for the right ear and two readings for the left ear. Participants will take 7 temperature readings over 24 h (6:00 am, 9:00 am, 12:00 pm, 3:00 pm, 6:00 pm, 9:00 pm, 12:00 am). Before each tympanic temperature measurement, participants will start with a 15-min rest on their back, without eating or drinking (59).

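### The fixed-time temperature day sits inside the 7-day actigraphy recording and constrains wake time or bedtime on one or two of the seven nights

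*Protocol article*

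**What the plan says.** Section 2.3.2 (Circadian rhythms assessments) describes two measurements. The sleep–wake cycle "will be continuously recorded over a 7-day" by wrist actigraph. This recording supplies TST, SOL, WASO, SE and the fragmentation index, and the rhythm measures L5, M10, IS, IV and RA.

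Tympanic temperature "will be recorded over a 1 day, during the actigraphy period". On that day "Participants will take 7 temperature readings over 24 h", at 6:00 am, 9:00 am, noon, 3:00 pm, 6:00 pm, 9:00 pm and midnight. Before each measurement, "participants will start with a 15-min rest on their back". Each measurement consists of two readings per ear.

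The clock times are the same for everyone and are not tied to habitual sleep. The article does not say which of the seven days is used, and it sets no nights aside. Section 2.3 schedules the circadian assessments at visits 2, 3 and 4. Section 2.7 names sleep and circadian rhythm variables among the hypothesised outcomes of both ANOVAs.

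**The concern.** The actigraphy week is meant to capture habitual sleep and rest–activity rhythm. A participant who takes the 6:00 am and midnight readings as instructed does not sleep as usual on the adjoining night or nights, because the measurement limits when sleep can end or begin.

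This matters because a shift in sleep timing is an effect the trial expects. The Introduction says early morning light advances the clock, and section 2.4.2 gives light between 8:00 and 10:00 am. If an intervention moves bedtime, wake time or sleep duration, a night bounded by a fixed reading shows that change only in part. IS describes regularity from day to day, so one atypical day among seven works against what it measures.

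**Working it through.** **Inputs from section 2.3.2.** Seven recorded days; one temperature day within them; seven listed times (the list agrees with the stated count of 7); 15 min supine before each reading; readings taken by the participant, who must therefore be awake.

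**Bounds imposed.** Latest wake time: 6:00 am − 15 min = 5:45 am. Earliest bedtime: midnight, or a few minutes later once four readings are taken.

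**Which nights are touched.** This depends on where the series starts:
- Start at 6:00 am, end at midnight (span 18 h, the listed order): the 6:00 am reading cuts short the night before, and the midnight reading delays the night after. Two nights, each bounded at one end.
- Start at any other listed time (span 21 h): midnight and 6:00 am bound the same night. One night, with at most 5 h 45 min = 345 min of unbroken sleep opportunity.

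Share of nights: 1/7 = 14.3% or 2/7 = 28.6%.

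**Size, under assumptions.** The article gives no habitual sleep times, so 8-h windows (480 min) are assumed, with no sleep before the midnight reading and no return to sleep after 6:00 am.

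Loss = (midnight − habitual bedtime, if positive) + (habitual wake time − 5:45 am, if positive). Effect on the 7-night mean = loss / 7.

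| Assumed habit | Bedtime delay (min) | Earlier waking (min) | Loss (min) | Loss / 7 (min) |
|---|---|---|---|---|
| 21:30–05:30 | 150 | 0 | 150 | 21.4 |
| 22:00–06:00 | 120 | 15 | 135 | 19.3 |
| 23:00–07:00 | 60 | 75 | 135 | 19.3 |
| 24:00–08:00 | 0 | 135 | 135 | 19.3 |
| 00:30–08:30 | 0 | 165 | 165 | 23.6 |

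From 22:00–06:00 to 24:00–08:00 the loss is constant, because 480 − 345 = 135 min. Allowing an assumed 6 min for the four readings after midnight gives 141 min, and 141/7 = 20.1 min. The total is the same whether it falls on one night or is split over two.

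**Daytime rests.** 7 × 15 = 105 min of imposed lying down. Two of these rests (5:45 am and 11:45 pm) fall when many participants would be in bed anyway. The other 5 × 15 = 75 min is 0.7% of the 7 × 24 × 60 = 10,080 min recorded, so this part is negligible over the week.

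**The case against.** **The arms are treated alike.** This stands. The article describes one schedule without variation by arm or visit, and section 2.7 compares pre/post change between groups, so a common shift largely cancels. A reader might infer a bias in the treatment contrast; the document gives no ground for that.

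**The loss is nearly constant.** This partly stands. The assumed windows spread only from about 19 to 24 min on the 7-night mean, so differences in habitual timing add little noise. Differences in who goes back to sleep, or who follows the midnight reading, add more, but the article offers nothing to size them.

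**The figure is a ceiling under its assumptions.** This stands. Someone already up by 5:45 am, or still awake at midnight, is unconstrained at that end. Participants may doze again, or recover sleep on other nights. Lost opportunity is not lost sleep in people with sleep complaints: at an assumed 80% efficiency, 20 min becomes 16 min. Going back to sleep shrinks the TST loss but moves the disturbance into WASO and fragmentation.

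**The affected nights still carry information.** This stands. A reader might infer that 14% to 29% of nights show no treatment effect at all. In the listed order each night is bounded at one end only, and SOL, WASO, SE and fragmentation can still respond. Nor does any calculation give a size for an effect on IS or IV, and IV is listed as a within-day measure.

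**The full protocol may drop these nights.** It may, and an article commonly leaves such rules out. The point does not rest on that silence: the article itself fixes both the overlap and the clock times.

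**Conclusion.** The point holds as a limited measurement problem. As scheduled, the temperature series constrains one or two of the seven actigraphy nights. It distorts absolute levels, adds some noise and partly masks effects on sleep timing and duration.

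For an assumed 8-h sleeper with no return to sleep, mean sleep opportunity over the week falls by about 20 min, or about 24 min for a 00:30 to 08:30 habit. The true TST loss is likely smaller. That actigraphic TST, SOL, WASO and SE are averaged over the seven nights is inferred; the article uses the word average only for L5 and M10.

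The reach is confined to actigraphy and to any sleep diary kept on the same days. Sleep is also measured by polysomnography and questionnaires, and nothing in the article places the polysomnography night next to the temperature day. The change is worth making because it is cheap, not because the trial's main comparison is at risk.

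**What to change.** Amend section 2.3.2 in one of two ways, identically at every visit and in every arm:

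1. Leave the temperature day, and the night or nights bounded by its midnight and 6:00 am readings, out of all actigraphy sleep and rhythm variables. Extend wear by one or two days if seven clean nights are wanted.
2. Schedule the series so that neither the midnight nor the 6:00 am reading falls on a recorded night. For example, start at 9:00 am after the seventh night and end at 6:00 am the next day, with the analysed actigraphy window closed before the first reading. Placing a 6:00 am to midnight day directly before or after the week is not enough: the 6:00 am reading would still end the last recorded night, or the midnight reading would delay the first.

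As a precaution, state that the home polysomnography is not recorded on an affected night.

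The cost is wording and scheduling, plus either 5 or 6 usable nights instead of 7 or one or two more days of participant burden.

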#### Physical fitness assessment

2.3.3

Muscular strength and cardiovascular capacities will be tested to assess physical fitness.

The evaluation of maximal hand grip strength will be recorded using a hand dynamometer (Takei A5401 Hand Grip Dynamometer Digital, Takei Scientific Instruments Co., Japan). Three successive measurements will be collected in a standardized position: participants will be seated on a chair without armrests, clenching their hands around a dynamometric handle. Their hand will rest on their leg to relax their shoulders and avoid elbow movements. The force developed in isometry by the gripping force of the hand will be recorded in kilograms.

The evaluation of maximal leg extension power will be recorded using the Nottingham Power Rig (Medical Engineering Unit, University of Nottingham Medical School, Nottingham, United Kingdom), specifically designed for older adults (60). Eight successive measurements will be collected in a standardized position for the right leg only. Participants will adopt a seated position with arms bent over the torso and will perform a maximal foot push to a large foot pedal. The power developed at the maximal speed of the flywheel after the pedal push, measured in watts, is recorded (60).

Peak Oxygen uptake (VO_2_ peak) will be measured with a maximal incremental test on a bicycle ergometer (eBIKE COMFORT, General Electric HealthCare) under medical supervision. Participants will follow a 3-min warm-up at 30 watts and will be instructed to pedal for as long as possible while the load will increase by 20 watts every 2 min. Developed power, and O_2_ and CO_2_ flow rates will be recorded before the test (resting values), at each level (relative values), until the end of the test (maximal values), and during the following 3 min of passive recovery (recovery values). Heart rate (HR) and electrocardiogram will be continuously recorded to track possible cardiac irregularities and stop the protocol if necessary. Criteria for reaching a VO_2_ peak (61) will include achieving a plateau in heart rate and VO_2_ recordings, inability to follow the imposed pedaling velocity, or reaching a given resistance. The main recorded parameters will include maximum oxygen uptake (mL/min/kg), maximum aerobic power (W), maximum HR (bpm), and respiratory quotient measured during the test.

#### Motor fitness assessment

2.3.4

Motor fitness will be assessed through tests of balance and functional mobility.

Postural static balance will be assessed using a standard static force platform (SPS system, Synapsys, Marseille, France), with dimensions of 50 × 50 × 17.5 cm. After removing their shoes, participants will be required to place their feet apart, forming an angle of 30°, in the middle of the platform. Two trials with eyes open (EO) and two trials with eyes closed (EC), each lasting 30 s, will be performed in a static position. For each condition, the sway area (mm^2^) and the Standard Deviation (mm) of the sway of the center of pressure will be analyzed along the Medial-Lateral (ML) and Anterior–Posterior (AP) axes. The Romberg quotient (RQ) will be calculated to evaluate the role of visual information in static balance, representing the ratio between the surface parameter of the center of pressure with EC to the one measured with the eyes open EO. Also, the maximal limit of the stability test will be recorded without time limitation (mm^2^). In this test, participants, with their eyes open, will swing as far as possible in all directions while keeping their bodies straight and without moving their feet or falling. The researcher will stop the test when the participant no longer improves their limits of stability.

Functional mobility will be assessed using the Timed Up and Go (TUG) test (62, 63). The performance time will start when the participant will begin to move to stand up and will end when the participant will sit down again. The participant will start by sitting on a chair with their feet on the floor and hands on their legs. At the “go” signal, they will stand up, walk 3 meters, turn around a cone, walk back, and sit down again. Two trials at a self-paced speed and two as fast as possible will be performed and measured in seconds.

#### Cognitive assessment

2.3.5

Cognitive executive functions will be evaluated using tests from the GREFEX battery (64). Inhibition will be assessed using the Stroop Color-Word Interference test (65). Mental flexibility will be assessed using the Trail Making Test (TMT) (52). The dual-task performance will be assessed using Baddeley’s dual task (66). Long-term memory will be assessed with a computerized task based on the memory game principle (67). This task, adapted from Rasch et al. (67), will evaluate the consolidation of visuospatial learning during sleep and will involve memorizing 12 pairs of cards. Learning will be considered achieved when 67% of the responses will be correct (a total of 8 pairs out of 12). A recall will be proposed the next morning after the night’s polysomnography. The number of pairs of cards correctly retrieved after learning and after the night’s sleep will be collected to calculate a rate of improvement or forgetfulness during the night.

#### Quality of life and mood assessment

2.3.6

QoL will be evaluated using the SF-36 Health Survey (68), which is based on eight physical and mental health domains: physical function, role-physical, bodily pain, general health perceptions, vitality, social functioning, role-emotional, and mental health. The Global Physical Activity Questionnaire (GPAQ) will evaluate participants’ physical activity through different behavioral domains, including work, transport, and leisure (69).

Mood symptoms, including anxiety and depression, will be assessed using the State–trait Anxiety Inventory (STAI state subscale and STAI trait subscale) (70), Visual Analog-Anxiety Scale (VAS) (71), and Geriatric Depression Scale (GDS) (72, 73).

### Interventions

2.4

PET and HE interventions will be delivered via videoconferencing using a secure web-based platform named SAPATIC (Santé Activités Physiques Adaptées utilisant les Technologies de l’Information et de la Communication developed by Mooven, Montpellier, France). BLE and GVS interventions will involve remote monitoring using a web-based platform. All participants will be able to connect to the platform at home and will have access to the planning and follow-up of their interventions. All participants’ data will be hosted on an authorized health data host.

#### Physical exercise training (PET)

2.4.1

PET, designed according to the World Health Organization (WHO) and the American College of Sports Medicine (ACSM) guidelines (74), will be supervised by qualified physical trainers. Participants will follow a 12-week home-based physical exercise training intervention with the objectives of improving muscular function and aerobic capacity and maintaining autonomy. The intervention will consist of two 60-min aerobic sessions per week via videoconferencing (with real-time coaching) and one 60-min self-guided strength training session per week (without real-time coaching), totaling 36 sessions. PET sessions will be scheduled in the early afternoon. Participants will be provided with a step bench for performing different exercises before starting the physical exercise training intervention. Heart rate monitoring (OnRythm 500^®^) will also be provided to each participant to monitor the intensity level of physical effort. The target heart rate will increase over the weeks, starting at 60% of their reserve heart rate (determined during the VO2 peak test) and reaching 75% at the end of the intervention. Perceived pain, fatigue, and well-being (visual analog scales) will be evaluated at each session (videoconferencing and self-guided sessions) before, during, and after sessions. Perceived exertion (Borg rating) will be evaluated after each session. This information will enable the professional to ensure that the work is performed at the targeted intensity while adapting to the participant’s tolerance.

The two collective videoconferencing sessions per week will consist of aerobic exercises (i.e., run/walk on the spot, jumping jacks, step, or dance). Each 60-min PET session will consist of a verbal contact sequence, warm-up exercises (5–10 min), aerobic exercises (40 min), a cool-down period (5–10 min), and finally, a verbal feedback sequence. The number of repetitions and exercise difficulty will gradually increase during the sessions, modulated according to the participant’s capacities at the time of the exercises. The physical trainer will progressively increase activity difficulty in duration, then frequency, and ultimately intensity only if the participant tolerates previous increases. The sessions will be limited to 5 participants, enabling the physical trainer to adapt the exercises to each individual.

The self-guided sessions will focus on resistance exercises to increase arm, leg, and whole-body muscle strength (i.e., series of ventral/back/side plank, wall sit, pumps, lunges, squats, or front/side raises). Participants will receive a booklet containing detailed instructions for each exercise. Core training sessions will last 40 min, with the remaining 10–15 min equally allocated to warm-up and cool-down. The booklet will provide variations for each exercise to increase difficulty.

#### PET combined with bright light exposure (BLE)

2.4.2

Participants in the BLE group will receive the same remote exercise training intervention as the PET group. The PET intervention will be supplemented with 12 weeks of bright light exposure sessions at home. Each participant will be provided with a light lamp (DAYVIA^®^ 072, France) and will be instructed to self-administer light sessions 5 days a week (from Monday to Friday) for 1 h in the morning (between 8:00 am and 10:00 am). During the sessions, participants will face the 10,000-lux light box at a distance of 50 cm and 45° from the eyes, avoiding direct staring to minimize discomfort. The intervention will be remotely monitored on the SAPATIC digital platform, in specific: exposure days, exposure time, and remarks filled in by the participants.

#### Galvanic vestibular stimulation (GVS)

2.4.3

Galvanic Vestibular Stimulation (GVS) is a non-invasive method used to stimulate the vestibular system. The GVS paradigm involves the bilateral bipolar mode, with the anode electrode placed on the mastoid bone behind one ear and the cathode electrode behind the other ear.

Bipolar galvanic stimulations will be delivered by the mini-CT portable box (Soterix Medical^®^, United States). Participants will self-administer five sessions per week at home (from Monday to Friday) over 2 weeks, each lasting 20 min. The intensity will be set to 1 mA, initiated by a 60-s ramp-up and terminated by a 60-s ramp-down (52). Each session will be scheduled at the same time in the morning.

The researcher will program the GVS device before the intervention, configuring it according to the specified parameters and generating 10 unique session codes for each participant, corresponding to the 10 stimulation sessions. Throughout the intervention, participants will be instructed to enter only the code assigned to the day’s session. The quality of skin-electrode contact will be systematically checked, and if the signal is deemed “poor,” the stimulation will not initiate. The electrodes will be pre-soaked in saline solution, to minimize cutaneous sensations. The first vestibular stimulation session will be conducted in the laboratory with the experimenter, after which participants will be guided to self-administer subsequent sessions at home. The intervention will be remotely monitored through the SAPATIC digital platform.

#### Control group-health education (HE)

2.4.4

The participants in the active control group will attend a one-hour health education session each week for a total of 14 weeks. These videoconference sessions will cover topics such as the benefits of physical activity, healthy lifestyles (including sleep habits and dietary balance), and cardiovascular risk factors. The inclusion of an active control group will aim to mitigate any potential influence of social contact and motivational factors on performance differences between the groups.

### Data collection and management

2.5

The participants to be included will be registered with an identification number, ensuring anonymity for all collected data. Trained staff will collect the data under the supervision of the principal investigator. The data will be stored on a separate hard disk and processed anonymously. Each identification code will correspond to a laboratory file, documenting test results from baseline, before, and after interventions. Documentation of each physical training session will be collected and saved on the secure web-based platform (SAPATIC^®^). The balance between benefits and risks is favorable, with minimal adverse events observed for PET (muscular pain or contractures; risk of cardiovascular problems; risk of falling), BLE (headache, eye strain, nausea), and GVS (nausea, dizziness, swaying sensation, metallic taste in the mouth). Any adverse events will be documented in a study monitoring register. To ensure data quality, a trained project assistant will review data entries and cross-check the digitized version once all training and assessments are completed.

According to the ethical registration, there will be no independent data safety monitoring committee for this study. The conduct and progress of the study will be continuously monitored by the principal investigators and scientists and will be audited by the sponsor at mid-study and the end of the study.

### Sample size calculations

2.6

The sample size calculation has been performed using R statistical software (R Core Team). In order to detect relevant differences between groups in the changes from pre-to post-intervention, we determined a sample size sufficient to detect medium effect sizes (Cohen’s *f* = 0.4). Therefore, α = 0.05, and *p* = 0.90, were selected to favor clinically significant effect sizes. The sample size calculation is based on sleep quality as the main variable. A total of 24 participants per group are necessary to examine the hypothesis that interventions impact sleep quality. Two additional participants are included to compensate for possible drop-outs. Each of the four groups will consist of 25 participants, resulting in a total of 100 participants.

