#### Sleep assessment

2.3.1

Participants will undergo a polysomnography (PSG) recording at home using a portable device (Embletta^®^ MPR Sleep System, NATUS, Orlando, United States). Ten electrodes will be placed over the scalp according to the international 10–20 system: frontal (F3 | F4), central (C3 | C4 | Cz), occipital (O1 | O2), ground (Cz | Fz), and a bi-mastoid reference (A1 | A2), with impedance kept below 15 kΩ. This montage will also include an electrooculogram (EOG), an electrocardiogram (ECG), and a chin electromyogram (EMG). Respiratory movements, airflow, and oxygen saturation will be recorded with abdominal and thoracic belts, nasal and oral thermistors, and finger pulse oximetry. The Electroencephalogram (EEG) signal will be digitized at a sampling rate of 256 Hz. High-pass and low-pass filters will be applied, respectively, at 0.3 Hz and 35 Hz. PSG recordings will be manually scored in 30-s epochs following the recommended standard criteria of the American Academy of Sleep Medicine (53) using RemLogic software. Sleep analyses will be conducted to calculate standard sleep parameters, including total sleep time (TST, min), sleep onset latency (SOL, min), wake after sleep onset (WASO, min), sleep efficiency (SE, %), percentage of time spent in each sleep stage (S1, S2, Slow-Wave Sleep, and Rapid-Eye Movement sleep, %), and apnea-hypopnea index (AHI). Sleep apnea will be defined by a ≥ 90% drop of nasal pressure for at least 10 s, whereas sleep hypopnea will be characterized by a ≥ 30% drop of nasal pressure for a minimum of 10 s, associated with an arousal or an oxygen desaturation of ≥3% (53).

Sleep quality and quantity will be evaluated using validated self-report questionnaires. Sleep quality and disturbances over the last month will be evaluated using the Pittsburgh Sleep Quality Index (PSQI) (49) through different parameters, including work, sleep habits, sleep disturbances, subjective sleep quality, the use of sleep medication, and trouble staying awake during the day. Daytime sleepiness will be assessed using the Epworth Sleepiness Scale (ESS) (54) and insomnia over the last month will be assessed with the Insomnia Severity Index (ISI) (55). Participants will complete a sleep diary to subjectively assess sleep quality and duration, including hours of bedtime, sleep quality, number, and duration of nocturnal awakenings and naps.

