### Statistical analyses

2.7

Data will be analyzed with R statistical software (R Core Team, Austria). The statistical analysis will determine the effects of the three different training interventions on sleep, fitness, cognitive, and quality of life variables compared to a control group. The analysis will include subjects who completed all the pre-and post-tests. If participants drop out or deviate from the intervention protocols, their data will not be used. Deviations will include non-eligibility, withdrawal of consent, missed test visits, and intervention protocol not completed. Data from the pre-test and post-test will be presented using descriptive statistics: mean, standard deviation, and percentage to describe the participants’ characteristics and performance on assessments. Comparisons within and between four groups at baseline and post-intervention will be done using repeated measures ANOVA, after checking for normality. Assessments will be considered as the dependent variables, and the group will serve as the independent variable. *Post hoc* analyses will be conducted when a significant main effect is observed using Tukey’s test to correct for multiple comparisons.

The initial ANOVA, comparing the PET, PET, and BLE, control group, will aim to assess the presence of intervention effects (pre/post). The hypothesis is that the combined PET and light interventions will result in improved outcomes in both groups compared to the control group across various domains, including physical and motor fitness, cognitive, QoL, circadian rhythms, and sleep variables.

The second ANOVA, comparing the GVS and control groups, will be designed to assess the existence of intervention effects (pre/post). The hypothesis is that the GVS intervention will lead to improvements in balance, cognition, QoL, circadian rhythms, and sleep variables compared to the control group.

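### The trial is sized on sleep quality, which is tied to no instrument or visit, and the only multiplicity correction (Tukey) does not reach across the sleep outcomes

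*Protocol article*

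**What the plan says.** Section 2.6 of the protocol article (Sample size calculations) states: "The sample size calculation is based on sleep quality as the main variable". On the error rates it says: "Therefore, α = 0.05, and *p* = 0.90, were selected". The effect size is Cohen's f = 0.4, and the result is given as: "A total of 24 participants per group are necessary to examine the hypothesis that interventions impact sleep quality". No instrument, parameter or visit is attached to the main variable.

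Sleep is measured in several ways:
- Section 2.3.1 (Sleep assessment), PSG: "Sleep analyses will be conducted to calculate standard sleep parameters, including total sleep time" and eight further parameters.
- Section 2.3.1, self-report: the PSQI, ESS and ISI, and a sleep diary.
- Section 2.3.2 (Circadian rhythms assessments), actigraphy: five sleep parameters, listed beside a "non-parametric circadian rhythm analysis".

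Section 2.7 (Statistical analyses) treats the assessments as dependent variables. It plans one ANOVA of PET, PET+BLE and control, and a second of GVS and control. The only multiplicity provision is Tukey's "test to correct for multiple comparisons", applied after a significant main effect.

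**The concern.** An alpha of 0.05 protects a claim only if it is clear which test carries that claim. Here the claim is that an intervention improves sleep quality, and the article does not use that term for one measure:
- The Introduction reports an effect of morning exercise on sleep quality as measured by PSG.
- Section 2.3.1 links both the PSQI and the diary to sleep quality.
- The Discussion treats a PSG sleep-latency result and an ISI result together as evidence that GVS affects sleep quality.

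A significant result on any of these could be reported as support for the main aim without departing from the text. PSG and questionnaire results that point in different directions could each be made the headline. Tukey does not prevent this, because it adjusts pairs of groups within one outcome. With two groups there is only one pair, so in the GVS comparison it adjusts nothing.

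**Working it through.** **The plan's own figure.** Inputs from section 2.6: f = 0.4, alpha 0.05, and 0.90 read as power. For a one-way ANOVA of change scores with k groups of n, the noncentrality is k × n × f². With k = 4 and n = 24 this is 4 × 24 × 0.16 = 15.36, and power is 91.2%. With n = 23 power is 89.8%. The stated 24 per group is reproduced for one four-group test of one variable at 5%.

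**Number of sleep variables.**
- PSG: TST, SOL, WASO, SE, four stage percentages, AHI = 9
- Questionnaires: PSQI, ESS, ISI = 3
- Actigraphy: TST, SOL, WASO, SE, fragmentation index = 5

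The total is 9 + 3 + 5 = 17 without the diary, or 12 without actigraphy.

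**Chance of at least one false positive, independent tests at 5%.**
- 17 variables, one ANOVA: 1 − 0.95^17 = 58.2%
- 12 variables, one ANOVA: 1 − 0.95^12 = 46.0%
- 34 tests, if all were independent: 1 − 0.95^34 = 82.5%

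**Correlated variables.** The documents give no correlations, so those below are assumptions. The figures come from null simulations with 24 per group, change scores, equal correlation among 17 variables and one control group shared by both ANOVAs. Ranges cover the two ANOVAs and repeated simulations.

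| Assumed correlation | Per ANOVA | Either ANOVA |
|---|---|---|
| 0 | 58% | 80–81% |
| 0.3 | 49–50% | 72–73% |
| 0.5 | 39–40% | 60% |
| 0.7 | 27–29% | 45–46% |
| 0.9 | 15–16% | 26–27% |

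The shared control is why the first row falls slightly below 82.5%.

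**Favourable direction only.** The table counts significance in either direction. For GVS against control, a false positive in the direction of benefit has chance 1 − 0.975^17 = 35% if the variables are independent, and about 19% at correlation 0.5. A single test would give 2.5%.

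**One named measure per ANOVA.** Each ANOVA then holds 5%. Jointly the error is up to 1 − 0.95² = 9.75%. Power at f = 0.4 for the ANOVAs actually planned:

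| | Three groups | Two groups (GVS) |
|---|---|---|
| Power, 24 per group, alpha 0.05 | 85.3% | 77.4% |
| n per group for 90%, alpha 0.05 | 28 | 34 |
| Power, 24 per group, alpha 0.025 | 77.6% | 67.5% |
| n per group for 90%, alpha 0.025 | 32 | 41 |

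**The case against.** The strongest reply is that sleep quality means the PSQI. Section 2.3.1 assigns sleep quality to the PSQI, daytime sleepiness to the ESS and insomnia to the ISI. The PSQI also defines eligibility, and the Discussion separates sleep quality from overall sleep. This makes the PSQI a natural candidate, but the article never says so. It links the diary to sleep quality as well, and it uses the term for PSG and ISI results. The PSQI also covers the last month, whereas the GVS course lasts two weeks.

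A reader might go further and infer that the plan declares 17 co-primary outcomes, each tested at 5%, with any one sufficient for success. The documents do not support that. Section 2.7 gives no significance level, so 5% per test is inferred from the only alpha stated, in section 2.6. No decision rule is written. Five of the 17 variables stand under circadian rhythms. Several others overlap strongly (sleep efficiency, total sleep time and wake time; the stage percentages), so the independence figures are upper values.

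Adjustment across secondary outcomes is commonly left to an analysis plan that is not shown, and its absence here is no fault. But this article invokes a main variable, sizes the trial on it and states its own correction. What it fixes is therefore open to criticism.

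**Conclusion.** The point stands in this form: the sizing variable has no instrument or visit, and the stated correction does not act across outcomes or across the two ANOVAs. The 5% level set in section 2.6 is therefore not held for the claim about sleep quality.

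The size depends on two inferences (each variable tested at 5%, any significant one taken as support) and on the unknown correlation. Over assumed correlations from 0 to 0.9, the error rate runs from 58% down to about 15% per ANOVA, and from about 80% down to about 26% over both. None of these settings reaches 5%. The finding is an undefined main variable, not a declared set of 17 primary outcomes.

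**What to change.** In sections 2.6 and 2.7, before results are seen:
- Name one sleep-quality measure and one visit as the confirmatory outcome for each aim: visit 3 for PET and PET+BLE against control, visit 4 for GVS against control. The PSQI global score is the natural candidate for the first. For the second, the sponsor should choose a measure whose recall window fits a two-week course.
- State whether 5% is held for each aim (up to 9.75% jointly) or split across the two. Holding it per aim is defensible because the Introduction sets out two separate aims, but the choice should be written down.
- Label all other sleep variables secondary or exploratory. Either give an adjustment, such as the false discovery rate, or make no confirmatory claim from them.

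No new data are needed. There are two costs. A positive result on another sleep variable can no longer be the headline. The power must also be restated for three-group and two-group ANOVAs, where 24 per group gives 85.3% and 77.4% at f = 0.4 and alpha 0.05, not 90%.
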